### Section: 12.3 Falls Recoding

#### Replace:

A fall is defined as any event that led to an unplanned, unexpected contact with a supporting surface. Falls resulting from pathologic fracture, major trauma or facial trauma, and/or unavoidable hazards such as transient ischemic attacks, chair collapsing or cerebrovascular accidents will be excluded. A faller is defined as the participants sustained at least one fall or more. Information about new falls while on study will be documented using form, included the date of fall and related-injury. The number of falls is accumulated. A copy of radiograph confirming the fracture will be obtained.

#### With:

A fall is defined as any event that led to an unplanned, unexpected contact with a supporting surface. Falls resulting from pathologic fracture, major trauma or facial trauma, and/or unavoidable hazards such as transient ischemic attacks, chair collapsing or cerebrovascular accidents will be excluded. A faller is defined as the participants sustained at least one fall or more. Information about new falls while on study will be documented using form, included the date of fall and related-injury. The number of falls is accumulated. **The cumulative incidence of fallers will be calculated as the total number of participants with first fall at each time point divided by the number of participants at risk.** A copy of radiograph confirming the fracture will be obtained.

### Section: 15.1 Primary Endpoint

#### Replace:

- (1) Change from month baseline at month 36 in femoral neck BMD;
- (2) Change from month baseline at month 36 in lean mass of left thigh;
- (3) Change from month baseline at month 36 in TUG test;
- (4) The number of falls during the 36 months.

#### With:

#### **Primary endpoint:**

**Primary endpoint is the number of falls at 36 months.**

## Section: 15.2 Secondary Endpoints

Replace:

- (1) Change from month baseline at month 36 in osteocalcin;
- (2) Change from month baseline at month 36 in deoxypyridinoline;
- (3) Changes from baseline at month 36 in estradiol;
- (4) Change from month baseline at month 36 in endometrial thickness;
- (5) Nature, frequency and severity of adverse events and their relationship to treatment.

With:

**Secondary endpoints:**

- (1) Change from month baseline at month 36 in femoral neck BMD;**
- (2) Change from month baseline at month 36 in lean mass of left thigh;**
- (3) Change from month baseline at month 36 in TUG test;**
- (4) Change from month baseline at month 36 in osteocalcin;
- (5) Change from month baseline at month 36 in deoxypyridinoline;
- (6) Changes from baseline at month 36 in estradiol;
- (7) Change from month baseline at month 36 in endometrial thickness;
- (8) Nature, frequency and severity of adverse events and their relationship to treatment.

## Section: 16.3 Statistical Analysis

Replace:

All the analyses used randomly assigned patients under the ITT principle. For patients missing data after the baseline, the LOCF approach was used to analyze the longitudinal data. Repeated-measures ANOVA analysis was carried out between two groups and four times (baseline, 12, 24 and 36 months). Within-subjects results was used *t*-test on the percentage change from the baseline value. The numbers of falls and adverse events were performed by chi-square test. All tests will be used two-sided and set at the 5% level.

With:

**All the analyses will use randomly assigned patients under ITT principle. For**

patients missing data after the baseline, the LOCF approach use to analyze the longitudinal data.

The numbers of falls and adverse events will perform by chi-square test. Kaplan–Meier analysis will be calculated in order to demonstrate differences in number of fallers over time. The time to first fall will be analyzed using a Cox regression analysis providing a 95% confidence interval.

Repeated-measures ANOVA analysis should be carried out between two groups and four times (baseline, 12, 24 and 36 months). Within-subjects results will be used *t*-test on the percentage change from the baseline value. All tests will be used two-sided and set at the 5% level.

**24. AMENDMENTS 2:**

Protocol Title: The effects and safety of Bushen Yijing Fang (BSYJF) reduces hip fractures risk factors in late postmenopausal women with osteopenia:  
A long-term follow-up, randomized, double-blind and placebo-controlled trial

**Major Amendment:** 10 Years Extension Phase

Amendment Date: 10 January 2002

Version number: Ver1.2

**Rationale:**

In the vast majority of cases, a hip fracture is a fragility fracture due to a fall or minor trauma in someone with osteoporotic bone. Risk factors of hip fractures observed are expected to be of long duration. However, BSYJF treatment was designed initially 36 months. Instead, a 10 year extension phase is added to explore the effect of transitioning from 36 months of treatment. The main objective of this extension phase is to evaluate if latent effects of BSYJF that might be lower fall rate and even hip fracture rate. In other words, 10 years extension follow-up of treatment cessation can be studied and is an accepted clinical approach.

**Introducing a 10 years extension follow-up phase:**

Active intervention will take place over 3 years until the end of 2004. After the trial, the recruited participants will be followed up in the 3rd, 6th, and 10th year to assess the latent effects of BSYJF interventions on fall and hip fracture incidence rate in late postmenopausal women.

**Description of Changes:**

Study purpose, design, excluded criteria, endpoints, statistical analysis and the schedule of assessments were updated to reflect this change in study design.

Additionally, the study staff will have access to unblinded safety and efficacy data to assess the benefit/risk profile while the study is ongoing in this extension phase.

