## 8.2 Blinding

The blinding codes will be given to the pharmacist to keep and cannot be broken unless in emergency situations during the study. The treatment arrangements will be made by the pharmacist in each site, be blinded to the participants' characteristics and be not involved in the number generation and recruitment process.

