## 9. DRUG ADMINISTRATION

### 9.1 Packaging and Formulation

All the participants will be received daily calcium carbonate 300 mg as the basic treatment. The participants will be orally given BSYJF capsules or placebo capsules (3 capsules per time, 3 times per day) for 36 months. All the capsules should package in identical plastic bottles (100 capsules per bottle) and subsequently delivered to the participants every 3 month at each clinical visit. All the participants will be told to take the capsules with element calcium before meal. The quality control for screening and verification of adherence to the protocol will perform by the supervisor. BSYJF/placebo will be manufactured, packaged, and distributed by Shuguang Hospital.

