#### 17.5 Interim Analysis and Stopping Guidelines

An interim analysis will be performed at month 12. Although this is a 3 year study, the primary analysis will occur after all subjects have had the opportunity to complete the month 12 study visit. In order to maintain the blind, study staff at the Office of Scientific Research and Teaching who have direct contact with the sites will have access to results from the interim and primary analyses only at aggregate level until all subjects have completed the study and the treatment assignments have been unblinded. The month 36 data will be analyzed separately at the end of the study.

The study staff at the Office of Scientific Research and Teaching will review the safety and efficacy data for BSYJF/placebo. If at any time there are safety concerns, the study staff will communicate the concerns with a coordinator. The start date will depend on the subject's accrual enrollment.

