| Setting                     | Two sites                                                                                                                                                                                                                                                                                                                                                                                                                                                                                                                                                                                                                                                                                                                                                                                                                                                                                                                                                                                                                                                                                                                                                                                                                               |
| Intervention time    | From 2000-01-01 To 2004-12-31                                                                                                                                                                                                                                                                                                                                                                                                                                                                                                                                                                                                                                                                                                                                                                                                                                                                                                                                                                                                                                                                                                                                                                                                    |

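### Amendment 2 opens unblinded safety and efficacy data to study staff during the extension without first requiring month-36 completion and database lock, and without reconciling Sections 8.2 and 17.5

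*Supplement*

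**What the plan says.** Amendment 2 adds a 10-year untreated follow-up and, under Description of Changes, provides for that period that "the study staff will have access to unblinded safety and efficacy data to assess the benefit/risk profile while the study is ongoing". The staff are not defined, and no starting condition is given.

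Two sections bear on this, and the amendment neither lists them as changed nor gives replacement text for them:

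- **Section 8.2:** the blinding codes are held by the pharmacist and "cannot be broken unless in emergency situations during the study".
- **Section 17.5:** Office staff who deal directly with the sites may see the interim and primary results "only at aggregate level until all subjects have completed the study and the treatment assignments have been unblinded".

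On timing:

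- The synopsis in Amendment 2 keeps the intervention window at "From 2000-01-01 To 2004-12-31", and Section 9.1 gives 36 months of capsules per woman.
- The amendment's introduction to the extension says "Active intervention will take place over 3 years until the end of 2004" and places the follow-up after the trial.
- Section 25 has eligible women entering the extension when the initial 36-month treatment phase ends.
- Section 5.1, as replaced by Amendment 2, runs the study to December 2014.

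No enrolment dates are given.

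**The concern.** Since Amendment 1 the sole primary endpoint has been the number of falls at month 36. Amendment 2 adds the number of falls at the end of the extension. Counting falls takes judgement: Section 12.3 excludes falls from major trauma and from hazards regarded as unavoidable, and the form in Appendix C asks for a perceived cause. No blinded adjudication is described. Staff who know arm results or individual assignments could, without intending to, alter how they prompt for falls, which falls they exclude and how hard they work to retain a woman. The planned analyses would not detect or correct such bias.

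The permission is open-ended and covers efficacy. If any women are still on blinded treatment when it takes effect, the primary endpoint is exposed. If none are, the extension endpoint is still exposed. This route is separate from the month-12 look in Section 17.5 and would remain if that look were changed.

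**Working it through.** **1. The plan's own end date.** Treatment ends 31 December 2004. Adding 120 months gives 31 December 2014, which matches Section 5.1 as replaced by Amendment 2. The match does not settle when the extension starts. If women enter one by one, the last finishes in December 2014; if all enter together after treatment, all finish then.

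**2. Room for staggered enrolment.** The intervention window is 1 January 2000 to 31 December 2004, or 60 months. Treatment lasts 36 months. 60 − 36 = 24 months at most between first and last enrolment.

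**3. Overlap if each woman enters at her own month 36 (the Section 25 wording).** Overlap = end of 2004 − (first enrolment + 36 months), taking the last blinded treatment to end in December 2004. First-enrolment dates are assumed:

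| First enrolment | First extension entry | Overlap (months) |
|---|---|---|
| January 2000 | January 2003 | 24 |
| July 2000 | July 2003 | 18 |
| January 2001 | January 2004 | 12 |
| July 2001 | July 2004 | 6 |
| January 2002 | January 2005 | 0 |

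**4. Share of treatment time exposed on that reading.** Assume enrolment from January 2000 and uniform accrual over A months. A woman enrolled t months after the first has t months of treatment left when the first enters the extension. The average of t is A/2, so the share is (A/2)/36.
- A = 12: 6/36 = 17%.
- A = 24: 12/36 = 33%.

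**5. Overlap if the extension starts only after all treatment ends** (the reading suggested by the introduction to the extension): 0 months and 0%.

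**6. Is there a conflict with Sections 8.2 and 17.5?** Both rules are tied to the study. If the study includes the extension, as the December 2014 end date and the amendment's own description of the study as ongoing suggest, Amendment 2 permits what both rules bar. If the study in Section 17.5 ends at month 36, and the extension starts after the last such visit and after unblinding, Section 17.5 is satisfied. No text states that sequence. Section 16.2 orders finalisation of the analysis plan before lock and unblinding, but the amendment does not tie its permission to that lock.

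**The case against.** The strongest reply is that the amendment describes a sequence: intervention ends, the trial ends, follow-up begins. On that view access limited to the extension cannot touch the month-36 endpoint. Section 17.5 speaks of analysing month-36 data at the end of the study, so its condition may already be met by then; it also covers only Office staff who deal with the sites. The extension has no treatment, its outcome is an additional endpoint, and women record their own falls. Lifting the blind after treatment is then a design choice.

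Much of this stands. A reader might infer that the extension does overlap blinded treatment and that the primary outcome is therefore not blind. The documents do not establish that: there are no enrolment dates, no stated date of first extension entry, and wording that supports a start after the trial.

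Three things are not answered:

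- The sequence is not secured either. Section 25 can be read as entry woman by woman, the 60-month window allows staggered enrolment, and Section 17.5 itself expects accrual over time. No waiting period is planned for early finishers.
- Nothing in the amendment makes access wait for the last month-36 visit or for lock.
- Self-recording does not remove staff from the extension outcome. Falls are collected at scheduled contacts in years 3, 6 and 10, and the exclusions in Section 12.3 still have to be applied.

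**Conclusion.** The point holds in conditional form. Amendment 2 grants undefined staff unblinded safety and efficacy data with no requirement that month 36 is complete and locked. It leaves Sections 8.2 and 17.5 standing, and conflicts with them if the study includes the extension.

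The overlap with double-blind treatment lies between 0 and 24 months. The exposed shares of 17% and 33% rest on entry at each woman's own month 36, enrolment from January 2000 and uniform accrual over 12 or 24 months; none of these is stated as fact in the plan. If the extension starts only after all treatment ends, the share is zero and the primary endpoint is not affected. A flat statement that the primary outcome is unblinded would go too far.

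The risk to the 10-year falls endpoint does not depend on the reading. Its size cannot be calculated from the documents.

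**What to change.** Replace the sentence in Amendment 2 with a rule along these lines:

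- No arm-level or individual unblinded data, whether efficacy or safety, reach staff who have contact with participants, or who collect or classify falls, until the last woman has completed month 36 and that database is locked. Safety data need to be named, because they too can reveal assignment.
- Any earlier benefit/risk review is done by existing staff without such contact.
- Those who collect or classify falls in the extension stay unaware of assignment throughout.
- The emergency code break in Section 8.2 is unchanged.

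Then reconcile Sections 8.2, 17.5 and 25 with the two Amendment 2 paragraphs (Description of Changes and the introduction to the extension), so that they agree on when the extension starts, what completing the study means now that it runs to December 2014, and which staff are covered.

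The cost is one rewritten sentence plus consistent wording in those places. The downside is that unblinded review by site-facing staff waits until the month-36 lock.

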### 13.3 Adverse Event Collection and Reporting

Any adverse events occurring after the first dose of study medication will be recorded in the subjects’ records and on the CRFs. Information about the occurrence of any adverse events will be sought at all scheduled visits. The investigator is responsible for ensuring that all adverse events observed by the investigator or reported by subjects if SAE occurs. The SAE is reported within 24 hours to the coordinator by completing a Serious Adverse Event Form (Appendix D). In addition, the investigator should ensure that all regulatory requirements are completed.

The following adverse event attributes must be assigned by investigator: diagnosis, signs or syndrome(s) (if known); dates of onset; severity; assessment of relatedness to BSYJF/placebo and action taken. The investigator may be asked to provide follow-up information, discharge summaries, and extracts from medical records or CRFs.

A subject may voluntarily withdraw from treatment due to what she perceives as an intolerable adverse event. If either of these situations arises, the subject

should be strongly encouraged to undergo an end-of-study assessment and be under medical supervision until symptoms cease or the condition becomes stable. Documentation of all such SAEs will be retained in medical records.

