### Section: 5.1 Study Design

Replace:

The study duration is from January 2000 to December 2004. Subjects will be randomly assigned to receive BSYJF (n=70) or placebo (n=70) with a 1:1 allocation ratio. The study will carry out at the two sites (Institute of Orthopaedics and Traumatology, Shanghai Academy of TCM; and Shuguang Hospital). A total of 140 participants will be selected from two sites to participate in the study.

With:

**The study will be carried out from January 2000 to December 2014, comprised of a 36 month treatment phase and followed by a 10-year extension phase without treatment.** Subjects will be randomly assigned to receive BSYJF (n=70) or placebo (n=70) with a 1:1 allocation ratio. The study will carry out at the two sites (Institute of Orthopaedics and Traumatology, Shanghai Academy of TCM; and Shuguang Hospital). **At the beginning of the study, a total of 140 participants will be selected from two sites to participate in the study.**

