**All the included participants will be asked to record every number of fall during 10 years extension follow-up.**

Section: 15.2 Secondary Endpoints

Add:

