| ECG                              |           | √        | √         | √         | √         |                     |                     |                      |
| B-ultrasound                     |           | √        | √         | √         | √         |                     |                     |                      |
| DDIPA                            |           | √        | √         | √         | √         | √                   | √                   | √                    |
| Adverse events                   |           |          | √         | √         | √         |                     |                     |                      |
| Others                           |           |          |           |           |           |                     |                     |                      |
| Drug dispensing                  |           | √        | √         | √         |           |                     |                     |                      |
| Drug return                      |           |          | √         | √         | √         |                     |                     |                      |
| Combined disease and Medications | √         |          | √         | √         | √         |                     |                     |                      |

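### Amendment 2 provides for a benefit/risk assessment during the 10-year extension, but its updated Table 1 schedules no adverse event or medication collection at Yr. 3, 6 and 10

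*Supplement*

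**What the plan says.** Amendment 2 turns the 36-month trial into one "followed by a 10-year extension phase without treatment" (Section 5.1 as amended). Its introduction says that participants will be seen in the 3rd, 6th and 10th year after the trial "to assess the latent effects of BSYJF interventions on fall and hip fracture incidence rate in late postmenopausal women". Its Description of Changes adds that study staff will have "access to unblinded safety and efficacy data to assess the benefit/risk profile while the study is ongoing in this extension phase". It does not say which period those safety data come from.

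Section 13.3, which Amendment 2 does not touch, states: "Information about the occurrence of any adverse events will be sought at all scheduled visits". It gives no end date.

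The updated Table 1 in Amendment 2 has columns for Yr. 3, Yr. 6 and Yr. 10. Falls and DDIPA are marked there. The rows "Adverse events" and "Combined disease and Medications" are marked through Mo. 36 and blank afterwards. The addition to Section 3.3 also asks for serum 25(OH)D at the three visits, although the table has no row for it.

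For falls the plan is fuller. The addition to Section 9 says: "All the included participants will be asked to record every number of fall during 10 years extension follow-up". Section 12.3, as replaced in Amendment 1, says: "Information about new falls while on study will be documented using form, included the date of fall and related-injury". The form in Appendix C has injury and fracture columns.

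**The concern.** The extension looks for latent effects after treatment stops. If staff are to judge benefit against risk in that period, late harm needs a scheduled place as well as late benefit. Falls and hip fracture are the outcomes that BSYJF is hoped to improve, so they do not supply the rest of a risk assessment. A site that follows the table would ask about falls and lifestyle at Yr. 3, 6 and 10 and about nothing else that bears on harm.

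Two further things are at stake:

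- **Deaths and hospitalizations.** Women aged 55 to 69 at entry would be about 68 to 82 after 3 + 10 = 13 years. Deaths will occur, and they affect who is still at risk of a fall when the falls comparison is made at the end of the extension.
- **Later drug use.** At entry the plan excludes recent users of estrogen, calcitonin, fluoride, bisphosphonates or adrenocortical hormone, and women on four or more prescription medicines. It therefore treats these as relevant. Its ban on self-supplied calcium and vitamin D covers only the 36 months (Section 17.2 as amended). After that, no scheduled row records what the women start taking.

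**Working it through.** The plan gives no figure on this point to reproduce. The check is a row count and a comparison of passages.

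1. **Rows in the updated Table 1.** There are 16 assessment rows, of which 12 are marked at Mo. 36. Of those 12, 2 (Falls and DDIPA) are marked at Yr. 3, 6 and 10, and 12 − 2 = 10 stop at Mo. 36. This point concerns two of the ten:

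| Row | Treatment phase | Extension |
|---|---|---|
| Adverse events | Mo. 12, 24, 36 | 0 of 3 visits |
| Concomitant disease and medication | Screening, Mo. 12, 24, 36 | 0 of 3 visits |
| Falls | Baseline, Mo. 12, 24, 36 | 3 of 3 visits |

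2. **Table against Section 13.3.** Yr. 3, 6 and 10 are columns of the schedule, so on a literal reading they are scheduled visits. Amendment 2 changes the Synopsis, Sections 3.3, 5.1, 6.2, 9, 15.2 and 17.2, and Table 1. Section 13.3 is not on that list. Text and table therefore disagree, and nothing says which governs.

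3. **Table against the Description of Changes.** Two readings are possible.
   - The safety data are to be gathered in the extension. The table then does not supply them.
   - The safety data are those of the treatment phase, seen unblinded during the extension. The table is then no obstacle, but the text does not say so, and the conflict in step 2 remains.

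   Either way an edit is needed.

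4. **What would still be collected.** Every fall, with date, injury and fracture fields and a radiograph to confirm a fracture; hip fracture incidence as a stated aim; and serum 25(OH)D. Part of this is risk information, but it does not cover harms unrelated to falls.

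5. **Other routes for deaths and hospitalizations.** Section 13.2 counts fatal events and hospitalizations as serious. Section 13.3 requires serious events to be reported within 24 hours. Section 13.4 asks sites for 3-monthly progress reports that include adverse events. None has a stated end date. They pass on what a site comes to know, and do not schedule a question to each woman. Section 14 does schedule annual follow-up for death and hospitalization, but only for women who stop the intervention and only for 36 months.

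6. **Timing.** The last marked adverse event contact is Mo. 36, when treatment ends. The next contacts are 3, 6 and 10 years later, so the gaps are 3, 3 and 4 years. Events still open at Mo. 36, or starting soon after, have no marked follow-up.

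**The case against.** The strongest reply is that the extension is not silent on risk. Falls and fractures can move in either direction, so they are not benefit data alone. The adverse event and serious event rules have no end date, and Amendment 2 does not revoke them. The benefit/risk sentence says when staff may see unblinded data, not when those data must arise, and the 36-month safety data fit it. The extension is also off treatment, with falls as its one added endpoint, so a lean schedule is a defensible choice.

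Most of this stands, and it limits the point. A reader might infer that the extension will yield no new risk data at all. The documents do not support that, given the fall, injury, fracture and 25(OH)D data and the open-ended reporting rules. A reader might also count the blank ultrasound and hematology cells as the same fault. Section 12 sets its measurements, and Section 12.4 the laboratory tests, at baseline and months 12, 24 and 36, so I make no point of those cells.

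The reply does not remove the disagreement between Section 13.3 and the table. If Section 13.3 governs, the table is wrong, and sites that use it as their checklist will miss the data. If the table governs, the source of the safety data has to be named.

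**Conclusion.** The point holds as an unresolved conflict between text and schedule. Amendment 2 provides for a benefit/risk assessment during the extension, and Section 13.3 seeks adverse events whenever a visit is scheduled. The updated table marks neither adverse events nor concomitant disease and medication at any of the three extension contacts. If sites follow the table, new risk information will be largely confined to falls, fall-related injury and fracture, and the extension could say little about other late harm.

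The size is 0 of 3 extension visits for each of the two rows. By the schedule, adverse events are sought in 3 of 13 years. A reader might turn that fraction into a gain in precision by pooling all 13 years of follow-up. The documents do not support such a figure. It would join treated and untreated years under one event rate, assume that every woman is followed to the end, and assume complete capture that three recall contacts cannot give.

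The conclusion assumes that sites work from the table. The documents do not settle whether the table or Section 13.3 governs, or which safety data the benefit/risk sentence means.

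**What to change.** Reconcile the passages in one of two ways.

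- **Collect the data.** In the updated Table 1, mark "Adverse events" and "Combined disease and Medications" at Yr. 3, 6 and 10. Limit the first to major events by history: deaths, hospitalizations, new diagnoses, and the outcome of events open at month 36. Report both descriptively by randomised arm beside the falls result. Medication data would describe later drug use. Because that use begins after randomisation, recording it would not by itself separate it from a latent effect.
- **Narrow the claim.** State in the Description of Changes of Amendment 2 that the benefit/risk assessment rests on the 36-month safety data. Say that Section 13.3 applies to visits up to month 36, and limit the extension's conclusion to falls and fractures.

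The first option costs a table edit, a few history questions at three contacts already planned, and one more descriptive table. Its downside is recall over 3 to 4 years, which is adequate for major events and poor for minor ones. The second costs only wording, but gives up any statement on other late harm.
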